**Brasilia**

**January 2019**

**SUMMARY**

**INTRODUCTION:** The hypoglycemic role of some nutrients has been widely discussed in studies that especially evaluated the long-term effect. However, evaluating and discussing the acute glycemic effect of these nutrients is urgent in order to establish possible dietetic management to help patients with diabetes to control hyperglycemia, especially postprandial hyperglycemia. **OBJECTIVE:** To understand the acute glycemic response after the addition of different foods to the breakfast of patients with type 2 diabetes. **MATERIAL AND METHODS:** This is a crossover clinical trial with 22 patients with type 2 diabetes. They will perform a 120-minute glycemic curve after consuming breakfast with different foods showing varied nutritional characteristics and dosages: 3 g of cinnamon powder, 3 g of cinnamon in capsules; 6 g of cinnamon powder; 6 g of cinnamon in capsules; 100 g lettuce; 100 g of tomato; 30 ml olive oil; mixed salad with 50 g of lettuce, 50 g of tomato and 15 ml of olive oil; 150 g of avocado; 15 g of wheat bran; 15 g of chia seeds or 15 g of golden flaxseed flour, in random order. This research project is linked to the Doctoral Program in Health Sciences and Technologies at the Faculty of Ceilândia at the Universidade de Brasília. **EXPECTED RESULTS:** To understand the acute impact on the glycemic response after adding different foods in different dosages to a meal is essential to indicate effective types and quantities to achieve normoglycemia.

**KEYWORDS:** diabetes mellitus, glycemia, cinnamon, dietary fiber, fats.

1. **INTRODUCTION**

Diabetes mellitus (DM) is a disorder characterized by chronic hyperglycemia that affects 425 million people and was responsible for 4 million deaths worldwide (2017), 44.9% of which in people under 60 years of age (Cho *et al* , 2018). Brazil is the 4th country with the highest number of patients with diabetes; in the period from 2008 to 2010, diabetes was responsible for 12% of total hospitalizations and 15.4% of hospital costs in the Unified Health System (SUS) (Costa *et al*, 2017). Therapeutic adherence is the biggest challenge for those with the disease due to the major change in lifestyle imposed by the treatment itself (ADA, 2015). In Brazil, the prevalence of patients with diabetes with inadequate glycemic control varies between 69.3 and 73.1% (Lima *et al*, 2016; Moreira, 2016) and postprandial hyperglycemia (up to 120 minutes after meals) can contribute up to 70% of this picture (Riddle *et al*, 2011).

Managing hyperglycemia is a major challenge and many strategies to assist patients with diabetes in this task have been investigated. Several studies have observed hypoglycemic activity of specific dietary components, such as fiber, fat, or other nutrients (Ranasinghe *et al*, 2012; Shen *et al*, 2014; Dog *et al*, 2007; Ley *et al*, 2014; Gopal *et al*, 2017; Bol *et al*, 2016; Perera *et al*, 2012; Vuksan *et al*, 2017). Many studies have only investigated the hypoglycemic effect in the medium or long-term; however, glycemic reduction needs to be sought immediately when the patient notices hyperglycemia and the appropriate choice of food can greatly contribute to this objective (SBD, 2017; Farmer et *al*, 2007).

Cinnamon is a potential spice to be investigated, as several clinical trials have shown that consuming 1 to 6 g of cinnamon (Cinnamomum cassia) for a period of 40 days to 4 months reduced glycemic levels in patients with type 2 diabetes (Crawford, 2009; Khan *et al*, 2003; Mang *et al*, 2006; Akilen *et al*, 2010). However, the acute effect of cinnamon in the glycemic response in patients with type 2 diabetes after consuming different dosages, in the form of powder or in capsule, has not been investigated.

It is known that high fiber consumption for long periods reduces glycemia in patients with diabetes (Silva *et al*, 2013), but the acute glycemic effect after consuming different types of fiber in physiological amounts for a single meal (according to nutritional recommendations) is necessary to indicate the best dietary modification in the rapid search for normoglycemia (SBD, 2017). The consumption of chia, flaxseed, wheat bran and vegetables, such as lettuce, is associated with decrease in blood glucose level, but the their acute effect on postprandial glycemic response has not been studied (Vuksan *et al* , 2017; Boll *et al*, 2016; Gopal *et al*, 2017).

Food sources of healthy fats are also being investigated. Consumption of avocado plus olive oil for 4 weeks reduced blood glucose levels in women with type 2 diabetes. However, the acute glycemic response after consumption of avocado alone or of olive oil, or of olive oil with salad, has not been studied (Lerman-Garber et al, 1994*)*.

It is necessary and urgent to understand which foods and their dosages show a hypoglycemic effect to help patients with type 2 diabetes in the search for more rapid glycemic control. It is also worth highlighting that dietary approaches have a lower risk of intoxication or side effects compared to medications and can help these patients in the constant search for glycemic control, reducing the risk of polypharmacy, drug interactions and adverse effects, such as intoxication.

1. **OBJECTIVES**

**2.1 General:** To understand the acute glycemic response after adding different foods to the breakfast of patients with type 2 diabetes.

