**2.2 Specifics:**

**I)** To measure the glycemic response at times 0/15/30/45/60/90/120 minutes after consumption of the tested meals, which will be:

- Standard breakfast;

- Standard breakfast plus 3 g of cinnamon powder;

- Standard breakfast plus 3 g of cinnamon capsules;

- Standard breakfast plus 6 g of cinnamon powder;

- Standard breakfast plus 6 g of cinnamon capsules;

- Standard breakfast plus 100 g of lettuce;

- Standard breakfast plus 100 g of tomato;

- Standard breakfast plus 30 ml of extra virgin olive oil;

- Standard breakfast plus 115g of mixed salad containing 50 g of lettuce, 50 g of tomato and 15 ml of extra virgin olive oil;

- Standard breakfast plus 150 g of avocado;

- Standard breakfast plus 15 g of wheat bran;

- Standard breakfast plus 15 g of chia seeds and

- Standard breakfast plus 15 g of golden linseed flour;

**II)** – To check the effect of the tested meals on palatability;

**III)** To compare the time-to-time glycemic responses resulting from the evaluated meals and

**IV)** – To analyze the behavior of the curve and the area below the glycemic curve (at times 0/15/30/45/60/90/120 minutes) after consuming tested meals.

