**3.4 Intervention**

The intervention will take place from 05/01 to 08/30/2019.

Participants will measure their capillary blood glucose before leaving home and, if their blood glucose level is lower than 80 mg/dL or higher than 200 mg/dL, they will not participate in the intervention on that day, and another date will be scheduled. Subjects must arrive at the place where the intervention will take place (at the UPA of Núcleo Bandeirante) between 7:00 am and 8:30 am, and fasting for 8 to 11 hours. In the night before, everyone will eat two standard meals (dinner and supper).

In random order, they will be instructed to consume the standard breakfast, or a standard breakfast plus one of the test foods (foods that will be tested: 3 g of cinnamon powder; 3 g of cinnamon in capsules; 6 g of cinnamon powder; 6 g of cinnamon in capsules; 100 g of lettuce; 100 g of tomato; 30 ml of extra virgin olive oil; 115 g of mixed salad containing 50 g of lettuce, 50 g of tomato and 15 ml of extra virgin olive oil; 150 g of avocado; 15 g of wheat bran; 15 g of chia seeds or 15 g of golden flaxseed flour), within 15 minutes. After consuming each meal, participants will complete the Visual Analogue Scale (**ANNEX II**) to assess palatability, considering appearance, smell, texture, flavor and intensity of flavors (sweet, salty, bitter and sour) (Flint *et al.* , 2000). The glycemic curve will be monitored for 120 minutes at times 0, 15, 30, 45, 60, 90 and 120 minutes. Capillary blood glucose determination will be carried out using the Accu-Check Active device (Roche Diagnostics) made available by the researcher and will be the option of choice so that glycemic results are known quickly and the patient is not exposed to the risk of unmonitored hypoglycemia. The positive area formed below the glycemic response curve will be calculated using the trapezoidal method. Washout application will be for a minimum of 3 days and a maximum of 10 days.

Table 1 presents the nutritional information of the standard breakfast that will be offered to patients. The nutritional value corresponds to approximately 15% of the total energy value of a standard diet of 2,000 kcal, containing 59.4% carbohydrates, 28.6% lipids and 12.0% proteins and is in accordance with the Brazilian Diabetes Society Guidelines (2017).

Table 1. Nutritional information for the standard breakfast

| **Food** | **Quantity** | **CHO (g)** | **LIP (g)** | **PTN (g)** | **Fibers (g)** | **Lime** |

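### The four cinnamon meals form a complete amount-by-form 2 x 2, but section 3.5 fixes no amount or form contrast and leaves the question to single pairs of meals

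*Protocol*

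**What the plan says.** The Introduction states the gap for cinnamon directly: its acute effect "after consuming different dosages, in the form of powder or in capsule, has not been investigated". Section 3.4 then lists the meals that address it: "3 g of cinnamon powder; 3 g of cinnamon in capsules; 6 g of cinnamon powder; 6 g of cinnamon in capsules". Every participant takes all four, in random order, along with the standard breakfast and eight other additions.

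Section 3.5 gives two analyses of glucose. The area under the curve is analysed by one-way repeated-measures ANOVA across meals. The glucose values are analysed by two-way repeated-measures ANOVA with meal and time as factors. Both are followed by Bonferroni-adjusted post hoc comparisons. Neither model has a term for amount or form, and no subset of comparisons is named.

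On quantities in general, the Summary says that understanding the response "after adding different foods in different dosages to a meal is essential to indicate effective types and quantities to achieve normoglycemia", and the Introduction closes by saying "It is necessary and urgent to understand which foods and their dosages show a hypoglycemic effect". The mixed salad is "115 g of mixed salad containing 50 g of lettuce, 50 g of tomato and 15 ml of extra virgin olive oil", which is half of each portion given alone (100 g, 100 g, 30 ml).

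**The concern.** Cinnamon is the only food for which the design varies both amount and form, and it does so in a balanced way. A balanced 2 x 2 lets all four meals contribute to the amount question and all four to the form question. Treating the meals as unrelated levels gives up that gain: each question is split into two separate pairs, each using half of the data and each sharing a multiplicity penalty with comparisons that have nothing to do with cinnamon. A real difference between amounts or forms could then be missed, and a null result would say little.

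A secondary matter is how the results will be worded. The Summary's sentence could be carried into conclusions about quantity for foods that were given in only one portion, or into a reading of the salad as a combination effect.

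**Working it through.** **Inputs.** 13 meals (section 2.2); 22 participants and a 5% significance level (section 3.2); Bonferroni post hoc comparisons (section 3.5). The protocol gives no within-person SD, so results are in units of s, the within-person SD for one meal. Assumptions: equal and independent within-person errors, two-sided tests, 80% power, paired-test degrees of freedom (21).

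**The plan's own figure.** 19 x 1.15 = 21.85, rounded up to 22, as stated. The base figure of 19 cannot be re-derived, because effect size, SD and power are not given.

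**Count of comparisons.**
- Pairs among 13 meals: 13 x 12 / 2 = 78.
- Pairs among the four cinnamon meals: 4 x 3 / 2 = 6. Two compare amounts within a form, two compare forms within an amount, and two change both.
- Foods given alone in more than one amount: 1 of 8. The other seven (lettuce, tomato, olive oil, avocado, wheat bran, chia, flaxseed flour) have one amount each.

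**Variance per participant.** Write 6p, 6c, 3p, 3c for the four meals.
- One pair, 6p - 3p: s^2 + s^2 = 2s^2.
- Amount averaged over form, (6p + 6c)/2 - (3p + 3c)/2: 4 x s^2/4 = s^2.
- Form averaged over amount: also s^2.
- Interaction, (6p - 3p) - (6c - 3c): 4s^2.

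The standard error of the pooled contrast relative to one pair is sqrt(1/2) = 0.707, which is 29% lower. That equals doubling the participants for that question. The interaction's standard error is sqrt(4/2) = 1.41 times that of one pair.

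**Detectable difference, n = 22, 80% power.** The standardised paired difference needed (from the noncentral t) is multiplied by the SD of the contrast: 1.414s for a pair, s for a pooled contrast, 2s for the interaction.

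| Comparison | Bonferroni family | Standardised difference | Detectable difference |
|---|---|---|---|
| One pair | 78 | 1.054 | 1.49s |
| One pair | none | 0.626 | 0.89s |
| Pooled amount or form | 3 | 0.741 | 0.74s |
| Pooled amount or form | none | 0.626 | 0.63s |
| Interaction | 3 | 0.741 | 1.48s |

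Of the fall from 1.49s to 0.74s, pooling takes it to 1.05s (1.49 x 0.707), and the smaller family does the rest. If the ANOVA's pooled error term (12 x 21 = 252 df) is used, the first row becomes about 1.3s.

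**Salad.** Let the portion given alone be 1 unit of each food. The five relevant meals are then (0,0,0), (1,0,0), (0,1,0), (0,0,1) and (0.5,0.5,0.5). An additive, linear model has 4 parameters and can be fitted (rank 4). Allowing curvature and pairwise interactions gives 10 parameters on 5 meals (rank 5), so amount and combination cannot be separated.

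**The case against.** The strongest reply is that the planned post hoc tests already answer the question. Ordinary pairwise comparisons include 3 g against 6 g in each form and powder against capsules at each amount, all within person. That stands: a reader might infer that amount and form are never tested directly, and that would be wrong. They are tested, but only pair by pair.

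A second reply is that choosing contrasts is often left to a statistical analysis plan. Here section 3.5 does fix the models and the post hoc method, so the omission lies in what the protocol specifies. The 78-pair family is nevertheless a reading, since 3.5 names no subset.

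Third, the pooled contrast changes the question. It equals the powder-specific effect only if there is no interaction, and the interaction itself is poorly estimated. This stands and is the real price of the proposal. The 29% also depends on equal, independent errors, and the protocol sets no precision target for cinnamon, so the gain is in efficiency and repairs no invalid test.

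On quantities, a reader might infer that the trial promises dose-finding for every food, or a combination effect for the salad. The document does not support either. The general objective is "To understand the acute glycemic response after adding different foods to the breakfast of patients with type 2 diabetes", and the third specific objective is "To compare the time-to-time glycemic responses resulting from the evaluated meals". Neither these nor the other objectives mention dose-response, a minimum amount or synergy. The Summary can be read as each food at its own stated amount, and every portion has a valid comparison with the standard breakfast.

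**Conclusion.** The point holds as a concrete improvement to the cinnamon analysis. For the gap that the Introduction names, the planned method has a standard error about 1.4 times that of a contrast available from the same data. The detectable difference is about 1.5s against 0.74s if the post hoc adjustment covers all 78 pairs. Without any adjustment on either side it is 0.89s against 0.63s. These figures rest on 22 completers, 80% power, two-sided tests and equal, independent within-person errors. The interaction remains weak under any choice.

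The wording part is minor. For seven of eight foods the trial can say whether the tested portion changes the response, but it cannot compare amounts. A null result for one of them cannot separate an ineffective food from too small a portion. The salad can be judged against the standard breakfast, but its difference from lettuce, tomato or oil alone mixes amount with combination. None of this makes the planned meal-versus-standard comparisons invalid.

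**What to change.** In section 3.5, add prespecified within-person contrasts for the cinnamon meals, beside each meal versus the standard breakfast:
1. 6 g versus 3 g, averaged over form.
2. Powder versus capsules, averaged over amount.
3. The amount-by-form interaction, reported with its confidence interval as a low-precision check.

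State the multiplicity family for these three, separately from the comparisons with the standard breakfast. State also that the form-specific and amount-specific pairs will be shown, and that the averaged contrasts will be read cautiously if the interaction estimate is large.

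In the Summary, limit the quantity statement to the portion tested versus the standard breakfast, with amounts compared for cinnamon only. Add a sentence that the salad's difference from its single components will not be read as a combination effect.

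The cost is three contrasts on data already planned and a few words of text, with no extra meals, visits or participants. The downsides are that the averaged contrasts answer a slightly different question from the single pairs, and that the stated claim becomes narrower.

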**2.2 Specifics:**

**I)** To measure the glycemic response at times 0/15/30/45/60/90/120 minutes after consumption of the tested meals, which will be:

- Standard breakfast;

- Standard breakfast plus 3 g of cinnamon powder;

- Standard breakfast plus 3 g of cinnamon capsules;

- Standard breakfast plus 6 g of cinnamon powder;

- Standard breakfast plus 6 g of cinnamon capsules;

- Standard breakfast plus 100 g of lettuce;

- Standard breakfast plus 100 g of tomato;

- Standard breakfast plus 30 ml of extra virgin olive oil;

- Standard breakfast plus 115g of mixed salad containing 50 g of lettuce, 50 g of tomato and 15 ml of extra virgin olive oil;

- Standard breakfast plus 150 g of avocado;

- Standard breakfast plus 15 g of wheat bran;

- Standard breakfast plus 15 g of chia seeds and

- Standard breakfast plus 15 g of golden linseed flour;

**II)** – To check the effect of the tested meals on palatability;

**III)** To compare the time-to-time glycemic responses resulting from the evaluated meals and

**IV)** – To analyze the behavior of the curve and the area below the glycemic curve (at times 0/15/30/45/60/90/120 minutes) after consuming tested meals.

**3 . MATERIAL AND METHODS**

**3.1 Experimental design:** the research is designed as a *crossover clinical trial* .

3.2 Description and selection of the population and sample: 22 subjects with type 2 diabetes treated at the Health Centers of Núcleo Bandeirante, Riacho Fundo I or Candangolândia will participate in this study. They will be invited to participate by putting up posters and giving lectures to publicize the study that will take place at the UPA of Núcleo Bandeirante. The sample size was defined considering the results of the study of De Carvalho *et al.* (‎2017) and the calculation was made by the *G Power* program version 3.1.9.2 (University of Düsseldorf, Germany), which indicated the need for at least 19 participants in each experimental group, to which we added 15% to compensate for possible losses. A significance level of 5% was adopted.

The inclusion criteria will be: to have a diagnosis of type 2 diabetes (American Diabetes Association , 2017); age between 30 ≥ and < 60 years; to consume breakfast regularly (≥ 100 kcal ingested, within 2 hours after waking up, on ≥ 4 days of the week); to be not allergic to the foods tested/used in the study; to agree to eat all study foods; to report no sleep disorders or use sleeping medication; to have availability of time to participate in all meetings within a period of up to 3 months and to agree to participate in the research by signing the Free and Informed Consent Form (TCLE).

Subjects that will be excluded from the study are those who: use exogenous insulin or medications for pathologies other than DM2; have complications from diabetes; smoke; have gastrointestinal disorders or irregular intestinal rhythm; have psychiatric disorders with impaired understanding; participate in other research protocols; refuse to provide or are not able to provide relevant data to the research and who do not attend previously scheduled tests for three times after confirming their presence in the day before the intervention.

3.3 Initial interview

Volunteers will participate in an initial interview to collect the following data: age, education, anthropometry, smoking, time since diabetes diagnosis, use, type and dosage of medications, presence of allergy and/or food intolerance, intestinal function, number of hours of sleep and self-reported sleep quality, breakfast and fiber consumption habits (**ANNEX I**).

Body weight will be determined using a digital electronic scale and height will be measured using a vertical anthropometer. The body mass index (BMI) value will be calculated and classified according to the recommendations of the World Health Organization (WHO, 2003) . Waist circumference will be measured by determining the midpoint between the lowest rib and the iliac crest, with a flexible and inelastic measuring tape (Heyward & Stolarczyk, 2000). Participants will also undergo body composition assessment using the double emission X-ray densitometry (DEXA) method before and after the end of the intervention.

Volunteers will be instructed to follow individualized nutritional prescriptions, to abstain from alcohol and physical exercise in the 24 hours prior to participating in the research.

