**3.6 Risk assessment:**

The risks arising from participating in the research are: to show any gastrointestinal symptoms or variations in blood glucose, including hypoglycemia. However, the volunteers' blood glucose will be constantly monitored and, if there is any complication, they will be directed to the Emergency Care Unit that operates in the same location (UPA Núcleo Bandeirante).

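### Two X-ray body scans are planned, but the criteria do not exclude pregnancy, the risk list omits the exposure, and the second scan has no stated purpose

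*Protocol*

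**What the plan says.** Section 3.3 (Initial interview) has participants' body composition assessed by the "double emission X-ray densitometry (DEXA) method before and after the end of the intervention". No participant is exempted.

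Section 3.2 plans for "22 subjects with type 2 diabetes" and sets the age criterion as "age between 30 ≥ and < 60 years", with no restriction by sex. The exclusions cover those who "use exogenous insulin or medications for pathologies other than DM2; have complications from diabetes; smoke; have gastrointestinal disorders or irregular intestinal rhythm", and also those who "have psychiatric disorders with impaired understanding; participate in other research protocols; refuse to provide or are not able to provide relevant data to the research". Repeated non-attendance at confirmed visits is the only other exclusion. Pregnancy does not appear. It is also absent from the interview data listed in section 3.3 and from the Annex I questionnaire.

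Section 3.6 states: "The risks arising from participating in the research are: to show any gastrointestinal symptoms or variations in blood glucose, including hypoglycemia". The rest of that section deals with glucose monitoring and referral to the emergency unit on the same site. It does not mention X-rays.

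The general objective is "To understand the acute glycemic response after adding different foods to the breakfast of patients with type 2 diabetes". Specific objectives I to IV concern glucose at fixed times, palatability, and the glycemic curve and its area. Section 3.5 describes sample characterization data and palatability by mean and standard deviation, and analyses glucose, its area under the curve, and appetite scores. It does not mention body composition.

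**The concern.** Three sections that should agree do not. Section 3.3 imposes an X-ray procedure twice. Section 3.2 has no criterion that keeps a pregnant woman from it. Section 3.6 sets out the risks of taking part without mentioning it. In addition, nothing in the objectives or the analysis section says what the second scan is for.

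This is a matter of participant protection and of agreement within the protocol. Someone applying the criteria and Annex I exactly as written would have no prompt to ask about pregnancy before either scan. A reader of section 3.6, such as an ethics committee, would not learn from it that X-ray exposure is part of the trial. The benefit that should justify the second exposure cannot be judged while its purpose is unstated.

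**Working it through.** The protocol gives no figure to reproduce on this point. The check is a count and a comparison of sections.

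**Number of scans.** Inputs are 22 participants (section 3.2) and 2 scans each (section 3.3).
- Planned total: 22 × 2 = 44, of which 22 are before and 22 after the intervention.
- This is a ceiling. Section 3.2 takes 19 as the required number and adds 15% for losses: 19 × 1.15 = 21.85, rounded up to 22. If only 19 complete, there are 19 second scans and 22 + 19 = 41 in all. The range on the protocol's own allowance is therefore 41 to 44.

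**Time between the scans.** Objective I lists 13 meals, which gives 12 intervals between visits. With the minimum washout of 3 days in section 3.4, the series lasts at least 12 × 3 = 36 days. Section 3.2 allows up to 3 months. A pregnancy could therefore begin between the two scans, so a check at entry alone would not cover the second.

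**Could the existing criteria exclude pregnancy indirectly?**
- Age 30 to under 60, both sexes: includes women who could be pregnant.
- Insulin use, medication for other conditions, complications of diabetes: would catch some pregnant women incidentally, but not one who meets none of these.
- Annex I: covers identification, anthropometry, smoking, medicines, allergies, food tolerance, bowel function, sleep and breakfast habit. There is no item on pregnancy, and none on sex.

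A pregnant woman with type 2 diabetes who uses neither insulin nor medication for another condition, and has no complications, can meet every criterion.

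**Risk list against procedure.** Section 3.3 imposes X-ray densitometry. Section 3.6 introduces its content as the risks of participating and names two kinds, gastrointestinal and glycemic. The X-ray exposure is in the first section and not in the second.

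**Use of the scans.** None of objectives I to IV names body composition. In section 3.5 the only heading that could take in a scan is the description of the sample. A baseline scan fits there naturally, although the protocol does not say so. A before-and-after comparison is not described anywhere.

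**The case against.** Several points can be made for the plan, and some of them limit the conclusion.

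- **The second scan may have a use.** A reader might infer that it answers no question and must be deleted. The protocol does not support that. Section 3.3 has volunteers follow individualized nutritional prescriptions and the series may last up to 3 months, so a second measurement could show whether body composition stayed stable. A statistical analysis plan was not available and might use it. What stands is that its purpose is not stated.
- **Effect on the glucose results.** A reader might infer that pregnancy during the series would distort the meal comparisons. No passage supports a claim about its effect on glucose handling, and section 3.4 randomizes meal order, so a drift in one participant would mainly add noise. The point does not rest on this.
- **Consent.** A reader might infer that participants are not told about the X-rays. That cannot be concluded, because section 3.2 requires a signed consent form and its text is not visible. The form may mention radiation or pregnancy. Even so, sections 3.2 and 3.6 and Annex I would remain as they are.
- **Likelihood.** The case needs a pregnant woman with type 2 diabetes who passes the restrictive exclusions and volunteers for 13 visits. Nothing shows this to be likely among 22 participants. The protocol gives neither the number of women of childbearing age nor a radiation dose. This limits any statement about the size of the harm, but it does not close the gap in the criteria.

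**Conclusion.** The point holds as a gap in eligibility, an incomplete risk list and an unexplained measurement. The clearest mismatch is between sections 3.3 and 3.6: one imposes an X-ray procedure that the other leaves out of the risks. The criteria in section 3.2 and the questions in Annex I leave pregnancy unaddressed.

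Its size is up to 44 scans, of which up to 22 have no stated purpose (19 if losses match the protocol's allowance). These counts measure exposure, not harm. The size of the harm cannot be estimated from the protocol.

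The conclusion rests on reading section 3.6 as the full list of risks, which is how it is worded, and on the visible text of section 3.2 and Annex I. It gives no reason to doubt the sample size, the area-under-the-curve analysis or the control of error.

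**What to change.** 1. **Section 3.2 and Annex I:** add pregnancy to the exclusion criteria. Put a direct question about it in the initial interview and repeat the question before each scan, because the second follows the first by at least 36 days.
2. **Section 3.6:** add the X-ray exposure to the risks so that the section agrees with section 3.3. Check that the consent form says the same.
3. **Section 3.3:** either state the purpose of the end-of-intervention scan or drop it. If it stays, name the matching objective or descriptive use.

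The cost is wording in three sections and one added question in Annex I, asked again before each scan. A few otherwise eligible volunteers may be lost. If the second scan is dropped, change in body composition over the series can no longer be described. None of the stated objectives asks for that description.
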